### **6.1.9 Magnetic Resonance Imaging Volumetric Measures**

All patients will undergo MRI scans to evaluate safety and potential treatment effects. Imaging sequences will be performed as per the MRI Imaging Manual.

Global and regional brain volumes and regional cortical thickness will be derived from the vMRI sequence and will include cross-sectional absolute measurements and longitudinal volume change. Most of the regional cortical thicknesses will include anatomical areas that are most affected in FTD. Additionally, white matter lesions will be quantified in a longitudinal manner.

All MRI data collected (Screening and during treatment period) will be sent to the central imaging laboratory for quality control, image processing and analysis, and archiving. The MRI scan evaluation at Screening and post-dosing will be performed by the central imaging laboratory.

## **6.2 Safety Assessments**

### **6.2.1 Adverse Events**

#### **6.2.1.1 Definitions of Adverse Events**

An AE is defined as any unfavorable and unintended sign (e.g., an abnormal laboratory finding), symptom, or disease temporally associated with the use of a drug, without any judgment about causality or relationship to the drug. Patients will be instructed to contact the Investigator at any time after enrollment into the study (i.e., after signing the consent form) if any symptoms develop.

After signed written informed consent is provided but prior to ICM administration of investigational product, only AEs and SAEs related to a protocol-mandated intervention will be reported. All other AEs and SAEs during this time period will be recorded as medical history. After the ICM administration of investigational product, all AEs and SAEs will be reported.

A TEAE is defined as any event not present before exposure to investigational product or any event already present that worsens in either intensity or frequency after exposure to investigational product.

The Investigator is responsible for reporting all TEAEs (and predose AEs and SAEs related to a protocol-mandated intervention) that are observed or reported during the study, regardless of their relationship to investigational product or their clinical significance. Where known, a diagnosis should be recorded rather than individual signs, symptoms, or laboratory results.

Treatment-emergent AEs that may be associated with corticosteroid use should also be monitored ([Section 6.2.2.2](#)).

Adverse events may include:

- Any abnormal laboratory test results (hematology, blood chemistry, or urinalysis) or other safety assessments (e.g., ECG, radiological scans, vital sign measurements, C-SSRS), including those that are accompanied by clinical symptoms, considered clinically significant in the medical and scientific judgment of the Investigator (i.e., not related to progression of underlying disease), or require a medical intervention or change in concomitant medications.
- Exacerbation of a chronic or intermittent pre-existing condition including either an increase in frequency and/or intensity of the condition.
- New conditions detected or diagnosed after study intervention administration even though it may have been present before the start of the study.
- Signs, symptoms, or the clinical sequelae of a suspected overdose of a concomitant medication. Such overdoses should be reported regardless of sequelae.

Adverse events DO NOT Include:

- Any clinically significant abnormal laboratory findings or other abnormal safety assessments which are associated with the underlying disease, unless judged by the Investigator to be more severe than expected for the patient's condition.
- The disease/disorder being studied or expected progression, signs, or symptoms of the disease/disorder being studied, unless judged by the Investigator to be more severe than expected for the patient's condition.
- Medical or surgical procedure (e.g., endoscopy, appendectomy); the condition that leads to the procedure is the AE.
- Situations in which an untoward medical occurrence did not occur (social and/or convenience admission to a hospital).
- Anticipated day-to-day fluctuations of pre-existing disease(s) or condition(s) present or detected at the start of the study that do not worsen.
- Prescheduled or elective procedure or routinely scheduled treatment was scheduled (or on a waiting list to be scheduled) prior to obtaining the participant's consent to participate in the study.

### **6.2.1.2 Serious Adverse Events**

The ICH definition of an SAE is any untoward medical occurrence at any dose that:

- results in death
- is immediately life-threatening (Note: Life-threatening refers to an event that places the patient at immediate risk of death. This definition does not include a reaction that, had it occurred in a more severe form, might have caused death)
- requires inpatient hospitalization or prolongation of existing hospitalization. (Note: The following hospitalizations will not be considered SAEs: hospitalization for respite care, hospitalization for a pre-existing condition where either the hospitalization was planned prior to the study, or an elective surgery AND the patient did not experience an AE)
- results in persistent or significant disability/incapacity
- is a congenital anomaly/birth defect

Important medical events that may not result in death, be life-threatening, or require hospitalization may be considered SAEs when, based upon appropriate medical judgment, they may jeopardize the patient or may require medical or surgical intervention to prevent one of the outcomes listed in this definition. Examples of such medical events include allergic bronchospasm requiring intensive treatment in an emergency room or at home, blood dyscrasias or convulsions that do not result in inpatient hospitalization, or the development of drug dependency or drug abuse.

### **6.2.1.3 Eliciting and Documenting Adverse Events**

Adverse events will be assessed from the time the patient signs the ICF until exit from the study. Only AEs and SAEs determined to be related to a protocol-mandated intervention will be reported from the time the patient signs the ICF until ICM administration of investigational product. After ICM administration of investigational product, all AEs and SAEs will be reported.

At every study visit, patients will be asked a standard nonleading question to elicit any medically related changes in their well being. They will also be asked if they have been

hospitalized, had any accidents, used any new medications, or changed concomitant medication regimens (prescription and over-the-counter medications).

In addition to patients' observations, AEs identified from any study data (e.g., laboratory values, physical and neurological examination findings, ECG and MRI changes) or identified from review of other documents (e.g., patient diaries) that are relevant to patient safety will be documented on the AE page in the eCRF.

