| 
 
Quantify PGRN levels in blood and CSF
 
 | 
 
Change from baseline in PGRN levels in blood at Months 1, 2, 3, 6, 9, and 12
 
Change from baseline in PGRN levels in CSF at Months 2 and 12
 
 |
| Secondary                                                                        |                                                                                                                                                                                                       |
| To evaluate the effect of PR006A on:                                                    |                                                                                                                                                                                                       |
| 
 
CDR plus NACC FTLD
 
                    | 
 
Change from baseline in CDR plus NACC FTLD at Months 6 and 12
 
                                                                                       |
| 
 
NfL levels in blood and CSF
 
           | 
 
Change from baseline in NfL levels in blood at Months 2, 6, 9, and 12
 
Change from baseline in NfL levels in CSF at Months 2 and 12
 
         |

[figure not shown]

[figure not shown]

|                                                                                            |                                                                                             |
|--------------------------------------------------------------------------------------------|---------------------------------------------------------------------------------------------|
| 
I
 
[REDACTED]
 | 
I
 
[REDACTED]
 |
| 
I
 
[REDACTED]
 | 
I
 
[REDACTED]
 |

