#### 4.1.1 Inclusion Criteria

Each patient must meet all of the following criteria to be enrolled in this study:

1. Men or women aged 30 to 80 years (inclusive), at the time of informed consent.
2. Body weight range of  $\geq 40$  kg (88 lbs) to  $\leq 110$  kg (242 lb) and a BMI of 18 to 34 kg/m^2.
3. Has symptomatic FTD as per investigator assessment (bvFTD, PPA-FTD, FTD with corticobasal syndrome, or a combination of syndromes are allowed for enrollment).
4. Score  $\geq 1$  and  $\leq 15$  on CDR plus NACC FTLD SB.
5. Stable use of background medications at least 8 weeks prior to investigational product dosing.
6. Carrier of a pathogenic\* *GRN* mutation confirmed by the central laboratory.

\*All null mutations including nonsense, frameshift, splice site mutations, and complete or partial (exonic) gene deletions:

- All previously published pathogenic mutations, with proven functional deleterious effect (selected missense mutations may be included provided they are known to be pathogenic)
  - All pathogenic mutations listed in Molgen FTD database (<http://www.molgen.ua.ac.be>)
  - All new mutations with low plasma PGRN level ( $<70$  ng/mL) based on central laboratory measurement.
7. Negative screening test for *Mycobacterium tuberculosis* (MTB) or documented negative MTB test within 1 year prior to Screening.

8. Age- and gender-appropriate cancer screenings are up to date and completed as per the Investigator's judgment and local standard of care prior to Screening.
9. Patient and/or patient's legally authorized representative (LAR) (where applicable by local regulation) has the ability to understand the purpose and risks of the study and provide written informed consent and authorization to use protected health information in accordance with national and local privacy regulations. The patient or LAR may also provide consent for future biomedical research in accordance with their national regulations; however, the patient may still participate in the study without providing consent for future biomedical research.

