10. Patient has a reliable study partner/informant (e.g., family member, friend) willing and able to participate in the study as a source of information on the patient's health status and cognitive and functional abilities (including providing input into the rating scales). The study partner should have regular contact with the patient (in person or via phone/video communication). The study partner must sign a separate partner informed consent form (ICF) indicating that she/he understands the study requirements and is willing to participate and attend study visits requiring study partner input.
11. Women of nonchildbearing potential must be either surgically sterile (hysterectomy, bilateral tubal ligation, salpingectomy, and/or bilateral oophorectomy at least 26 weeks before Screening) or post-menopausal, defined as spontaneous amenorrhea for at least 2 years, with follicle-stimulating hormone level in the post-menopausal range at Screening based on the central laboratory's range.
12. Men and women of childbearing potential (i.e., ovulating, premenopausal, and not surgically sterile) must use a highly effective method of contraception consistently and correctly for the duration of the study including the long-term follow-up. Highly effective methods of contraception are those that, alone or in combination, result in a failure rate of less than 1% per year when used consistently and correctly (i.e., perfect use) and include the following for participants of childbearing potential:
  - a. Combined (estrogen and progestogen containing) oral, intravaginal, or transdermal hormonal contraception associated with inhibition of ovulation
  - b. Oral, injectable, or implantable progestogen-only hormonal contraception associated with inhibition of ovulation
  - c. Intrauterine device

- d. Intrauterine hormone-releasing system
- e. Bilateral tubal ligation or bilateral tubal occlusion (performed at least 3 months prior to Screening)
- f. Vasectomized partner (performed at least 3 months prior to Screening)
- g. Sexual abstinence (no sexual intercourse)

Acceptable forms of contraception for male participants include:

- a. Sexual abstinence (no sexual intercourse)
  - b. History of vasectomy (performed at least 3 months prior to Screening)
  - c. Condom with spermicide used together with highly effective female contraceptive methods if the female partner(s) is of childbearing potential (see above for list of acceptable female contraceptive methods)

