#### **6.1.1 CDR Plus NACC FTLD**

The CDR has been widely used in Alzheimer therapeutic studies. It serves as both a functional assessment instrument and a global rating. The CDR plus NACC FTLD was developed in 2008 as a supplement to the CDR ([Knopman et al 2008](#)). It was designed to

assess the clinical status of patients across the FTLT spectrum of disorders. To capture key FTLT patient characteristics, the CDR plus NACC FTLT adds 2 domains to the CDR: 1) the Behavior, Comportment, and Personality domain; and 2) the Language domain. To complete the CDR plus NACC FTLT, both the study partner and the patient are interviewed using the same CDR semi-structured interview. The following method is used for calculating the CDR plus NACC FTLT in this study: CDR plus NACC FTLT SB is reached by adding each of the 8 domain scores together to yield a single score that ranges from 0 (no impairment) to 24 (severe impairment) ([Miyagawa et al 2019](#)). A CDR plus NACC FTLT global score will also be calculated as per the established method ([Miyagawa et al 2020](#)).

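### The adverse-event questions in Section 6.2.1.3 go to patients with symptomatic FTD and do not name the mandatory study partner, so symptomatic events may be under-ascertained early after dosing

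*Protocol*

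**What the plan says.** Protocol Section 6.2.1.3 sets the elicitation rule: "At every study visit, patients will be asked a standard nonleading question to elicit any medically related changes in their well being". The follow-on questions about hospitalization, accidents, and new or changed medication are put to the same person. Section 6.2.1.1 likewise tells patients to contact the Investigator if symptoms develop. No section directs that the study partner be asked about AEs.

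Section 6.2.1.3 also opens a second route: "In addition to patients' observations, AEs identified from any study data (e.g., laboratory values, physical and neurological examination findings, ECG and MRI changes"), together with review of other documents such as diaries.

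Inclusion criterion 10 (Section 4.1.1) makes a study partner mandatory, someone "willing and able to participate in the study as a source of information on the patient's health status and cognitive and functional abilities". On attendance, it asks only that the partner be "willing to participate and attend study visits requiring study partner input"; the protocol does not list those visits. Section 6.1.1 describes one partner interview, for the CDR plus NACC FTLD: "both the study partner and the patient are interviewed using the same CDR semi-structured interview". Section 2 gives its Year 1 endpoint as "Change from baseline in CDR plus NACC FTLD at Months 6 and 12".

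**The concern.** Criteria 3 and 4 admit behavioral-variant FTD, primary progressive aphasia and combined syndromes, with a sum of boxes from 1 to 15 on a scale that runs from 0 to 24. Some of these patients will have limited insight or limited language. A rule that puts an open question to them, without naming the informant the protocol requires them to have, does not use the best available source for symptoms.

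The early post-dose period carries most of the weight. Under Section 6.2.1.5 every AE within 1 month of the administration procedure counts as an adverse reaction, and the sum of adverse reactions is a primary safety endpoint (Section 7.1.1). Section 11.1.1 has the iDMC review the first 2 patients of a cohort at least 8 weeks after the second is dosed, before the remaining 3 are released and the next dose level opens. Section 5.5.1.3 relies on noticing sensory symptoms and decompensation of FTD symptoms. An event that is never elicited cannot be recovered in the analysis, so this is a protocol matter and not one for the SAP.

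**Working it through.** The protocol gives no event rate and no reporting fraction, so there is no figure of its own to reproduce. The check is a comparison of sections, a visit count and an illustration.

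**1. Sections side by side.** Criterion 10 defines the partner as a source on health status, with input to rating scales as one part of that role. Section 6.2.1.3 does not call on that source. The two do not contradict each other, but nothing turns the partner's stated role into an AE question.

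**2. Visit count (Table 13-1).** Scheduled post-dose visits in Year 1 are Days 1, 7, 14 and 21 and Months 1, 2, 3, 6, 9 and 12: 4 + 6 = 10. AEs are collected at all 10.

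- Visits where the visible partner-interviewed endpoint falls: Months 6 and 12, so 2.
- Visits with no explicit partner requirement: 10 − 2 = 8.
- Visits through Month 3: 4 + 3 = 7, of which 0 have an explicit partner requirement.

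The CDR row cannot be read in Table 13-1. One blacked-out instrument row has marks at Screening, Month 6, Month 12 and the unscheduled visit. That fits the endpoint timing but does not prove that this is the CDR row.

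**3. What else would catch a symptomatic event in the first month?**

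- 24-hour inpatient observation after dosing (Section 5.5.3).
- Vital signs at every visit, and laboratory tests at Days 7, 14 and 21 and Month 1.
- A physical examination at Day 14, which Section 6.12 makes brief and symptom-based.
- Neurological examination, TNAS and C-SSRS, each first repeated at Month 1. The TNAS is patient-reported (Section 6.18).
- A safety MRI at about Month 1 (Section 6.2.2.3).

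From discharge on Day 1 to Month 1, a symptom with no laboratory or vital-sign correlate is therefore recorded mainly if someone mentions it.

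**4. Illustration only.** Let p be the true rate of some symptomatic event by the time of review and s the share of such events that gets recorded. Both are assumptions. The chance that the review of 2 patients sees at least one case is 1 − (1 − p·s)².

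| p | s = 1 | s = 0.9 | s = 0.7 | s = 0.5 |
|---|---|---|---|---|
| 0.10 | 19% | 17% | 14% | 10% |
| 0.20 | 36% | 33% | 26% | 19% |
| 0.30 | 51% | 47% | 38% | 28% |

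For example, p = 0.30 and s = 0.7 give 1 − (1 − 0.21)² = 1 − 0.6241 = 0.3759. The table shows only how sensitive a 2-patient review is to incomplete reporting. It does not estimate what this trial would lose.

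**The case against.** The strongest reply is that the protocol already covers most of this. The partner is mandatory and a recognised source on health status, and nothing prevents a site from asking. AEs also come from study data and document review. Much of the primary safety endpoint (laboratory tests, vital signs, ECG, MRI, immunogenicity, sirolimus troughs, weight and waist) does not depend on what a patient says. Most stopping-rule events, such as hemorrhage, stroke, CNS infection or death, would reach the site through care or testing. Section 6.2.1.1 excludes expected disease signs from AEs unless they are more severe than expected, which narrows the behavioral events at issue. Section 6 leaves detailed instructions to study manuals that are not available here.

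Much of this stands, and it rules out three stronger readings that a reader might draw.

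- **That the primary safety endpoint rests on self-report.** It does not, given the measured components and the second AE route.
- **That partners will be absent from 8 of 10 visits.** The count is of visits without an explicit requirement. The visits needing partner input are unlisted, parts of the schedule are redacted, and partners may attend anyway.
- **That events are systematically under-counted, most of all in the most impaired patients, with a bias toward safety.** This is plausible, but no data in the protocol establish it.

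What the reply does not supply is the instruction itself. Without it, asking the partner is left to each site's habit in a multi-center study of 15 patients.

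**Conclusion.** The point holds as a gap in AE elicitation. Section 6.2.1.3 names the patient and not the partner, in a population where the protocol itself requires an informant on health status. On what is visible, 8 of 10 post-dose Year 1 visits, including all 7 through Month 3, carry no explicit partner requirement. Symptomatic AEs that leave no laboratory, imaging or examination trace (a headache, a sensory complaint, a brief seizure at home) may be under-ascertained when the adverse-reaction count and the 2-patient iDMC review depend on them. The objectively measured safety components are unaffected.

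The conclusion assumes that sites follow Section 6.2.1.3 as written and that no unseen manual adds the partner. The size of any loss cannot be derived from the protocol, and the percentages above illustrate assumed rates and reporting shares. This is a cheap improvement worth making, not an error that undermines the safety assessment.

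**What to change.** In Section 6.2.1.3, direct the standard nonleading question and the hospitalization, accident and medication questions to both the patient and the study partner at every visit, with the partner answering in person or by phone or video. In inclusion criterion 10, state that AE elicitation is an activity requiring partner input, so that the attendance wording covers it. Remote contact suits this study: the note to Table 13-2 already allows follow-up visits by telephone or video. Criterion 10 lets a partner keep in touch with the patient by phone or video only, and such a partner will see less, so it would help to record who supplied each report.

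The cost is protocol wording, a few minutes per visit with a partner who has already consented, and somewhat more AE data entry. Only data collection changes; no dose, visit schedule or stopping threshold is touched.

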#### **6.2.1.4 Reporting Adverse Events**

All AEs reported or observed during the study, as detailed in [Section 6.2.1.3](#), will be recorded on the AE page in the eCRF. Information to be collected may include but is not limited to the following:

- drug treatment
- dose
- event term
- time of onset
- Investigator-specified assessment of severity and relationship to investigational product
- time of resolution of the event
- seriousness
- any required treatment or evaluations
- outcome

Adverse events resulting from concurrent illnesses, reactions to concurrent illnesses, reactions to concurrent medications, or progression of disease states must also be reported. All AEs will be followed to adequate resolution. The Medical Dictionary for Regulatory Activities (MedDRA) will be used to code all AEs.

Any medical condition that is present at the time that the patient is screened but does not deteriorate should not be reported as an AE. However, if it deteriorates at any time during the study, it should be recorded as an AE.

